2.1 Study Overview

The overview of this study was to assess the clinical efficacy of acupuncture therapy in the treatment of Parkinson's disease-related constipation (PDC).

2.2 Background

Constipation is a non-motor symptom of Parkinson's disease (PD)(Bloem et al., 2021). More than 50% of PD patients experience constipation, which is an autonomic dysfunction characterized by anorectal disturbances and delayed colonic transit(Gan et al., 2018). Current research indicates that some PD patients experience constipation years before motor symptoms(Lesser, 2002). With the progression of PD, the prevalence of constipation increases, negatively impacting patients' quality of life. Constipation is developing into a significant problem in parallel with motor symptoms(Schapira et al., 2017).

Currently, increasing dietary fiber and fluid intake is commonly used to treat PDC(Barboza et al., 2015). When lifestyle changes are unhelpful, probiotics and prebiotic fiber, macrogol, and lubiprostone may be used, though these have limited evidence for treating PDC(Mozaffari et al., 2020). Constipation was recurrent and refractory in most PD patients, which requires maintenance therapy. As PD progresses, patients must switch to higher doses of anti-Parkinson's drugs to improve motor symptoms(Chou et al., 2018). Treating constipation with non-pharmacologic therapies is more appealing to patients with PD.

Acupuncture is a popular non-pharmacological treatment for gastrointestinal and neurological conditions, and it has been shown to be effective in treating constipation and PD in several studies(Li et al., 2022). However, high-quality clinical evidence on the efficacy of acupuncture for PDC is lacking. As a result, we created a randomized, single-blind clinical trial with sham acupuncture (SA) as a control to evaluate the efficacy of manual acupuncture (MA) for PDC.

2.3 Study Objectives

We designed a randomized controlled clinical trial to compare the efficacy and safety of manual acupuncture (MA) to sham acupuncture (SA) in the treatment of PDC.

2.4 Methodology

2.4.1 Trial design

This is a randomized, sham-controlled clinical trial aiming to examine the effect of acupuncture in the treatment of PDC. The cases in this study will be recruited from patients with PDC who meet the inclusion criteria in the outpatient department of Parkinson's disease at the First Affiliated Hospital of Guangzhou University of Chinese Medicine between May 2022 and November 2022. Participants will be fully informed of the study purpose, procedure, and related rights before the start of this study and will have signed an informed consent form to protect their rights, safety, and privacy.

The clinical trial has been approved by the Ethics Committee of the First Affiliated Hospital of Guangzhou University of Chinese Medicine (Ethics number: K-2022-005). The protocol has been registered with the China Clinical Trials Center (ChiCTR2200059979).

2.4.1.1 Pilot study and Sample size

We conducted a pilot study to determine the sample size for the randomized controlled trial. Twenty-eight patients were chosen to receive either manual or sham acupuncture (14 patients in each group). We used the change in weekly complete spontaneous bowel movements (CSBMs) from baseline to the end of the trial as an evaluation. Patients who received MA had a mean CSBMs score of 0.964 (standard deviation [SD],1.726), whereas patients who received SA had a score of -0.321. (SD, 1.310). According to PASS version 15.0, 31 patients are needed for each group at a two-sided significance level of 5% and a power of 90%. The sample size estimation was shown in Supplementary Figure S1. With an estimated loss-to-follow-up rate of 20%, we will plan to enroll a total of 78 patients with 39 patients per group.

[figure not shown]

**Supplementary Figure S1 Sample size estimation**

2.4.1.2 Randomization

An independent researcher will use the SPSS 26.0 procedure to generate the random number tables. 78 patients will be randomly assigned to the MA group and the SA group in a ratio of 1:1. The information about the assigned groups will be made into cards with the same shape and placed in opaque envelopes. When the patients start the clinical study, the envelopes will be opened and the groups will be formed according to the instructions on the randomized cards.

2.4.1.3 Blinding

This study will be blinded to patients, outcome assessors, and statisticians. The treatment time for patients in different groups will be set at different times of the day to prevent communication between the two groups. During the treatment, the patients will be required to wear an eye mask to ensure the implementation of the blinding method. All operations will be performed according to a standardized procedure to ensure consistency of operation. The efficacy assessor will not be involved in the grouping and treatment manipulation. The blinding will be removed at the end of the treatment, and patients will be informed of their grouping after treatment as well as will be told their type of acupuncture after follow-up.

This study will be controlled using a special acupuncture device which was developed and designed by our team members. The special acupuncture device was shown in Supplementary Figure S2. The acupuncture device consisted of a base, a cannula, and a specially designed acupuncture needle. There are classified into two types of bases. In the MA group, the base has a longitudinal opening at the bottom, through which acupuncture needles can be pierced into the skin. Conversely, the SA group's base has a closed adhesive with no opening at the bottom, so special flat-head needling can contact the skin through the adhesive but cannot pierce it. The cannula is removable and can be adjusted to meet the needs of various needling angles depending on the site of needling. The special flat-head needle has the same shank as ordinary acupuncture needle. Since the flat-head needle do not actually pierce the skin, it is designed to be shorter in length than ordinary acupuncture needle, and the length of the body exposed during needling is the same as that of ordinary acupuncture needle to ensure consistency of appearance during operation.

The special acupuncture device to be used in this study has been approved for a national utility model patent, with the patent number ZL202121352221.7 and is produced by a manufacturer with relevant qualifications (Guangzhou Suixin Medical Equipment Co., Ltd.). The related article has been published(Wang et al., 2022).

[figure not shown]

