2.4.5 Outcomes Measurements

2.4.5.1 Primary Outcome

**2.4.5.1.1** **The change of weekly complete spontaneous bowel movements (CSBMs).**

We use weekly CSBMs to observe changes in the number of bowel movements in patients with constipation. CSBMs are defined as the number of bowel movements that have occurred in the past 24 hours without the use of emergency medication. CSBMs are recorded by patients on an electronic bowel diary under the direction of an independent outcome assessor. Weekly CSBMs will be collected at baseline (week 0), post-treatment (week 4), and follow-up (week 8), and differences from baseline levels are compared at weeks 4 and 8.

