**2.4.5.2.2 Patient-Assessment of Constipation Quality of Life (PAC-QOL)**

The PAC-QOL is used to assess the quality of life of patients with constipation and consists of 28 items with 4 dimensions: physical discomfort, psychosocial discomfort, satisfaction, and worriedness and concerns. Each item's score ranges from 0 to 4. The total score ranges from 0 to 112, with lower scores indicating better quality of life in patients with constipation. The PAC-QOL will be rated at baseline, post-treatment, and follow-up.

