4.2.3 Operation method

The operation method will be referred to in the textbook Acupuncture and Moxibustion, edited by Wang Fuchun in 2021. The depth of acupuncture will be referred to in the textbook Meridian and Acupoints, edited by Shen Xueyong in 2021.

The patients will be placed in a supine position and wear an eye patch. The physicians will precisely locate the acupoints according to the standard, routinely disinfect the skin of the patients, paste the acupuncture device, adjust the cannula according to the application site, and take the needles to puncture the skin quickly and painlessly.

Table S3 displays acupoints with their insertion depth and direction. All acupoints will be left in place for 30 minutes before being removed, and the needle holes will be pressed for a few moments with a sterilized dry cotton swab when the needles are out. All patients will receive 12 sessions of treatment, three times a week (Tuesday, Thursday, and Saturday), for a period of four weeks.

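### The protocol fixes the time of unblinding inconsistently, so blinding of the week-8 primary and secondary outcomes is not secured

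*Protocol*

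**What the plan says.** Section 2.4.1.3 (Blinding) opens with "This study will be blinded to patients, outcome assessors, and statisticians" and gives no date on which this ends. Its first paragraph closes with one sentence in two parts that point to different times:

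- First part: "The blinding will be removed at the end of the treatment, and patients will be informed of their grouping after treatment".
- Second part: "as well as will be told their type of acupuncture after follow-up".

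Section 4.2.3 dates the end of treatment: "All patients will receive 12 sessions of treatment, three times a week (Tuesday, Thursday, and Saturday), for a period of four weeks". Section 4.3.3 sets the same course for the sham group.

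Outcome collection runs past that point. For the primary outcome, section 2.4.5.1.1 says "differences from baseline levels are compared at weeks 4 and 8", and on who records it, "CSBMs are recorded by patients on an electronic bowel diary under the direction of an independent outcome assessor". Section 2.4.5.2.2 says "The PAC-QOL will be rated at baseline, post-treatment, and follow-up", and CSEAS (2.4.5.2.1) and UPDRS (2.4.5.2.3) follow the same timing. Table S1 puts follow-up at week 8.

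Section 2.4.5.3 asks patients at the end of the trial to guess their assignment and whether the needle entered the skin. Table S1 marks the blinding assessment at week 0 and week 8, not at week 4.

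**The concern.** The sham device, the eye mask and the separate treatment times all serve to keep expectation out of outcomes that patients report themselves. The primary outcome is a diary count, and CSEAS and PAC-QOL rest on what patients feel and say. If patients learn at week 4 whether they had real or sham needling, the week-8 comparison can reflect that knowledge as well as the treatment. Week 8 is one of the two time points named for the primary outcome.

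Two further things are at stake. A patient who has been told the answer cannot give a meaningful guess, so the trial's only check on blinding would be lost. And the clause that lifts the blind names no one, so it does not clearly exempt the outcome assessors and statisticians whom the same section lists as blinded.

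**Working it through.** **1. The timing statements side by side**

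| Event | Time | Protocol location |
|---|---|---|
| Last treatment session | Week 4 | 4.2.3, 4.3.3 |
| Blind lifted, patients told their grouping | After treatment, so from week 4 | 2.4.1.3, first part of the sentence |
| Patients told their type of acupuncture | After follow-up, so after week 8 | 2.4.1.3, second part of the sentence |
| Second primary comparison of weekly CSBMs | Week 8 | 2.4.5.1.1, Table S1 |
| CSEAS, PAC-QOL, UPDRS repeated | Week 8 | 2.4.5.2.1 to 2.4.5.2.3, Table S1 |
| Patients guess their assignment | End of trial, week 8 | 2.4.5.3, Table S1 |

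Rows 2 and 3 are compatible only if grouping and type of acupuncture are different pieces of information. Section 2.4.1.2 defines two groups, manual acupuncture and sham acupuncture, and no coded label is described anywhere. On those definitions, telling a patient the group tells the patient the type. Row 2 then conflicts with row 3 and leaves row 6 without purpose. If a neutral code was meant, the statement that the blind is lifted at the end of treatment is still unqualified. No section says that anyone stays blinded through week 8.

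**2. The plan's own figure**

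The sample size does not depend on this point, but its inputs are used below. From section 2.4.1.1:

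- Difference: 0.964 − (−0.321) = 1.285 CSBM/week.
- Root-mean-square SD: √((1.726² + 1.310²)/2) = √((2.979 + 1.716)/2) = 1.532.
- Two-sample t-test, two-sided 5%: power 0.891 at 30 per group and 0.901 at 31 per group. The stated 31 reproduces.
- Allowance for 20% loss: 31/0.80 = 38.75, rounded up to 39 per group, 78 in total. This reproduces too.

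**3. Illustration of what disclosure at week 4 could do**

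The protocol gives no figure for reporting bias, so a range is assumed. Further assumptions are that patients learn real versus sham at week 4, that there is no true effect at week 8, and that the SD is 1.532. Let b be the between-arm difference in week-8 CSBMs produced by knowledge of allocation alone.

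- Standard error: SE = 1.532 × √(2/n), which is 0.389 at n = 31 and 0.347 at n = 39.
- Chance of a significant result favouring acupuncture: P(T > t₀.₉₇₅), where T is noncentral t with 2n − 2 degrees of freedom and noncentrality b/SE. The critical values are 2.000 (60 df) and 1.992 (76 df).

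| b (CSBM/week) | b as share of 1.285 | 31 per group | 39 per group |
|---|---|---|---|
| 0 | 0% | 2.5% | 2.5% |
| 0.10 | 8% | 4.4% | 4.7% |
| 0.25 | 19% | 9.2% | 10.6% |
| 0.50 | 39% | 24.3% | 29.6% |
| 0.75 | 58% | 47.5% | 56.9% |

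For example, at b = 0.50 and n = 31 the noncentrality is 0.50/0.389 = 1.28, which gives 24.3%.

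**The case against.** A reader might infer that the week-8 data are collected unblinded. The documents do not go that far. In a trial of real against sham needling, the type of acupuncture is the information that would bias self-report, and the sentence withholds it until after follow-up. The guess of assignment at the end of the trial also makes sense only if patients are still blinded then. Table S1 was read from a PDF, so its column alignment carries some risk, but section 2.4.5.3 gives the same timing in words. Blinding through week 8 may well have been intended. This objection stands: what is shown is a contradiction, not a settled plan to unblind at week 4. It does not remove the need for a correction, because a site that told patients their group at week 4 would be following the protocol as written.

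A reader might also infer that outcome assessors and statisticians lose the blind at week 4. The only disclosure described is to patients, and section 2.4.1.3 separately names assessors and statisticians as blinded and keeps the efficacy assessor out of grouping and treatment. Their unblinding is one possible reading of a clause that names no one. It is a gap to close, not an established fact.

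Finally, any single false-positive rate, such as 24% or 30%, could be taken as the size of the defect. It is not. The result depends strongly on the assumed bias and arises only under the adverse reading.

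**Conclusion.** The point holds as an internal contradiction that leaves week-8 blinding unsecured. Section 2.4.1.3 gives two incompatible times within one sentence, and the earlier one conflicts with the blinding questionnaire in section 2.4.5.3 and Table S1. Under the literal reading, disclosure precedes the week-8 CSBM count, the week-8 CSEAS, PAC-QOL and UPDRS, and the questionnaire itself. The week-4 comparison, the other primary time point, and the sample size are not affected.

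Confidence is high for the contradiction. No such confidence attaches to the size of any bias: the calculated range shows only that even modest reporting differences would matter at this sample size. The matter should be corrected because a primary time point is exposed, and it is not a detail that a statistical analysis plan would supply, since the protocol itself states when patients are told.

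**What to change.** In section 2.4.1.3, delete the clause that lifts the blind at the end of treatment, and replace the rest of that sentence with a single unblinding time. Suggested wording:

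*Each patient is told the allocated group and the type of acupuncture only after completing all week-8 assessments and the blinding questionnaire. Outcome assessors and statisticians remain blinded until week-8 data collection is complete for all patients and the database is locked.*

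The order matters: the questionnaire must come before disclosure, so section 2.4.5.3 and Table S1 should state that sequence too. Keeping the statisticians blinded until database lock goes slightly beyond resolving the contradiction, but it closes the gap left by the unqualified clause.

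The cost is a one-sentence amendment with matching notes in section 2.4.5.3 and Table S1. Patients learn their group about four weeks later than under the literal reading. Sample size, visits and analysis do not change.

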**Supplementary Figure S2 Details of the special device, acupuncture needles, and the angle of needle insertion.**

2.4.2 Diagnosis criteria

2.4.2.1Diagnostic criteria for Parkinson's disease

The diagnostic criteria for PD will refer to the Movement Disorder Society's revised clinical diagnostic criteria for Parkinson's disease in 2015(Postuma et al., 2015), which includes: there should be at least two supporting criteria, no absolute exclusion criteria, and no red flags. If one red flag is present, there must also be at least one supportive criterion and no more than 2 red flags are allowed for this category.

**2.4.2.1.1Supportive criteria**

(1) Clear and dramatic beneficial response to dopaminergic therapy. During initial treatment, patient returned to normal or near-normal level of function.

(2) Presence of levodopa-induced dyskinesia.

(3) Rest tremor of a limb, documented on clinical examination (in past, or on current examination).

**2.4.2.1.2 Absolute exclusion criteria**

(1) Unequivocal cerebellar abnormalities, such as cerebellar gait, limb ataxia, or cerebellar oculomotor abnormalities.

(2) Downward vertical supranuclear gaze palsy, or selective slowing of downward vertical saccades.

(3) Diagnosis of probable behavioral variant frontotemporal dementia or primary progressive aphasia, defined according to consensus criteria within the

first 5 years of disease.

(4) Parkinsonian features restricted to the lower limbs for more than 3 years.

(5) Treatment with a dopamine receptor blocker or a dopamine-depleting agent in a dose and time-course consistent with drug-induced parkinsonism.

(6) Absence of observable response to high-dose levodopa despite at least moderate severity of disease.

(7) Unequivocal cortical sensory loss, clear limb ideomotor apraxia, or progressive aphasia.

(8) Normal functional neuroimaging of the presynaptic dopaminergic system.

(9) Documentation of an alternative condition known to produce parkinsonism and plausibly connected to the patient’s symptoms, or, the expert evaluating physician, based on the full diagnostic assessment feels that an alternative syndrome is more likely than PD.

**2.4.2.1.3 Red flags**

(1) Rapid progression of gait impairment requiring regular use of wheelchair within 5 years of onset.

(2) A complete absence of progression of motor symptoms or signs over 5 or more years unless stability is related to treatment.

(3) Early bulbar dysfunction: severe dysphonia or dysarthria (speech unintelligible most of the time) or severe dysphagia (requiring soft food, NG tube, or gastrostomy feeding) within first 5 years.

(4) Inspiratory respiratory dysfunction: either diurnal or nocturnal inspiratory stridor or frequent inspiratory sighs.

(5) Severe autonomic failure in the first 5 years of disease. This can include: Orthostatic hypotension, Severe urinary retention, or urinary incontinence.

(6) Recurrent (>1/years) falls because of impaired balance within 3 years of onset.

(7) Disproportionate anterocollis (dystonic) or contractures of hand or feet within the first 10 years.

(8) Absence of any of the common nonmotor features of disease despite 5 years disease duration. These include sleep dysfunction (sleep-maintenance insomnia, excessive daytime somnolence, symptoms of REM sleep behavior disorder), autonomic dysfunction (constipation, daytime urinary urgency, symptomatic orthostasis), hyposmia, or psychiatric dysfunction (depression, anxiety, or hallucinations).

(9) Otherwise-unexplained pyramidal tract signs, defined as pyramidal weakness or clear pathologic hyperreflexia (excluding mild reflex asymmetry and isolated extensor plantar response).

(10) Bilateral symmetric parkinsonism. The patient or caregiver reports bilateral symptom onset with no side predominance, and no side predominance is observed on objective examination.

2.4.2.2 Diagnostic criteria for functional constipation

The Rome IV diagnostic criteria for functional constipation which published by the American Rome Committee in 2016 will be selected for the clinical diagnosis of functional constipation(Palsson et al., 2016).

(1) Two or more of the following must be met (a-e must be met at least once in every 4 bowel movements): (a) Straining to defecate. (b) Lumpy or hard bowel movements. (c) A feeling of incomplete defecation. (d) A sense of anorectal obstruction and/or obstruction. (e) Requires manual manipulation (e.g., finger-assisted defecation, pelvic floor support for defecation) to facilitate defecation. (f) Defecation less than 3 times per week.

1. Almost no loose stools without laxatives.
2. Inadequate conditions for the diagnosis of IBS.
3. Symptoms have been present for at least 6 months prior to diagnosis, and the above criteria have been met for the last 3 months.

2.4.3 Subjects

2.4.3.1 Inclusion criteria

(1) Meeting the Movement Disorder Society's revised clinical diagnostic criteria for Parkinson's disease in 2015.

(2) Meeting the diagnostic criteria for functional constipation in the Rome IV diagnostic Criteria.

(3) Between 35 and 80 years of age.

(4) Those with Hoehn-Yahr grade of Parkinson's disease ≤ 3.

(5) No medications taken within 2 weeks prior to treatment that may affect gastrointestinal function, such as prucalopride and probiotics.

(6) No participation in other clinical trials such as drugs or acupuncture within 1 month prior to inclusion in this study.

(7) Voluntary engagement in this study and ability to sign the informed consent.

(8) Good compliance, ability to understand the study content, and cooperation in the completion of the bowel symptom diary and scale filling.

2.4.3.2 Exclusion criteria

1. Noncompliance with inclusion criteria.
2. Having organic lesions of the digestive system (such as intestinal adhesions, obstruction, tumors or malformations in the gastrointestinal tract, etc.), or a history of abdominal or anorectal surgery that may affect intestinal transit, or systemic diseases that affect the dynamics of the digestive tract (such as diabetes mellitus, hyperthyroidism, etc.).
3. Serious life-threatening diseases such as severe cardiovascular and malignant tumors, etc.
4. Those who have skin lesions that are not inappropriate for needling, or those who have viscose allergy that prevent acupuncture device attachment.
5. Pregnant or lactating women.

2.4.3.3 Shedding and rejection criteria

A case is considered to be shed if any of the following criteria are met.

(1) Refusal to cooperate with the study arrangements for personal reasons and no longer suitable to continue the study after assessment.

(2) Sudden onset of serious illness, who is assessed to be unfit to continue with the study.

(3) The occurrence of a serious adverse event or an unexpected event.

(4) Those who withdraw from the study on their own.

A case is considered to be rejected if the following conditions are met.

(1) Those who have not completed treatment as required by this study, or the dose or dosing regimen of the anti-Parkinsonian drug need to be adjusted during treatment.

